**9.2. Number of people to include in the research and the statistical justification**

Without the OAS, 20% of the patients will have an oral accessibility score of at least 8.

The protocol hypothesizes that the use of the OAS will improves this frequency by 20% (*i.e*. 40% of patients will have a score of at least 8). To validate this hypothesis with an α of 5% and a power of 90%, a total of 140 patients is needed. When potential center-related and investigator-related effects and a study drop out rate of 10% are taken into account, the patient number rises to 200.

**A feasibility study** was conducted in the Department of Odontology of the CHR METZ-THIONVILLE over a period of 12 months (January to December 2009). During this period, 104 patients meeting the inclusion criteria of our study were aided by the Department of Odontology, which confirms the feasibility of the recruitment target that was set.

**9.3. degrée of planned statistical significance**

The α is fixed at 5%

**9.4. Statistical criteria for stopping the research**

None.

**9.5. méthod for taking into account missing, discarded, or invalid data**

Subjects without complete data will not be included in the comparative analysis of the oral accessibility scores. They will be described and compared to the subjects with complete data.

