**16. List of annexes**

**17. BIBLIOGRAPHIC REFERENCES**

**1.** PROTOCOL SUMMARY

| Title | *OAS: Evaluation of the effectivess and safety of an innovative medical device designed to enhance the oral accessibility of people with a handicap who have behavioral disorders: the Oral Accessibilty Spatula (OAS)* |
| --- | --- |
| Sponsor | *CHR METZ THIONVILLE* |
| Investigator Coordinator | *[name] [name]*  *Department of Odontology*  *CHR METZ-THIONVILLE – Bel Air Hospital*  *[name]*  *[contact] / Email: [contact]* |
| protocol version | *V4.0 produced 11/08/2017* |
| Justification/context | *It is sometimes difficult, even impossible, to access the oral cavity of people with a behavioral handicap. This is because of their defensive reflexes, where they spontaneously limit the amplitude of the mouth opening or keep their mouth open for very short periods only.*    *The currently available means of keeping the oral cavity open are often unsuitable for these patients and alternative devices have not been described in the literature.*  *This problem makes it difficult to perform preventive oral examinations or provide these patients with oral healthcare.* |
| Main Objective | *Evaluation of oral accessibility during the initial oral examination without and then with the oral accessibility spatula (OAS).* |
| Secondary Objectives | *Evaluation of the safety of the OAS*  *Evaluation of the tolerability of the examination without and with the OAS*  *Evaluation of operator comfort when using the OAS* |
| Primary Endpoint | *Visibility and probe-ability of the three tooth sectors (incisors/canines, premolars, and molars) during the examinations without and with the OAS, as indicated by using an Oral Accessibility Score (this score ranges from 0 = no accessibility to 12 = total accessibility)* |
| Secondary Endpoints | *Identification of adverse events and their frequency.*  *Venham Behavioral Rating Scale*  *Numerical scale measuring operator satisfaction* |
| Méthodology / Study design | *Prospective interventional study, multicenter, open-label*  *Only one visit is planned per patient.* |

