**5.1. Inclusion criteria**

- Minor or adult patient with am impairment accompanied with behavioral difficulties (known beforehand or discovered during oral examination)
- Score of 2 or more on the Venham Scale on a gradual approach to the oral cavity of the person (defined as touching the hand, then the lips, then attempting to spread the lips)
- The study-specific informed consent form is signed after the holders of parental authority over minor patients, the legal representatives of the minors and adults under guardianship, and the adult patients under trusteeship and their trustees are given information specific to the study

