**5.3. Procédure for premature STopping of the study or exclusion (stopping treatment + stopping follow-up)**

**5.3.1. Criteria and procedures for stopping treatment/medical device use and exclusion**

- *Premature stop criteria*

It is impossible to perform the evaluations, without and then with the spatula, due to patient behavior that involves their physical integrity (score of 5 on the Venham Scale).

- *Follow-up Methods for persons excluded from the study*

Patients with a score of 5 on the Venham Scale will be examined outside the study by using the following medical techniques:

- sedated by inhalation of an equimolar mixture of oxygen and nitrous oxide
- under sedation using Midazolam (intra-rectal or intravenous)
- Under general anesthesia if necessary.

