**9.7. choice of people to include in the analyses.**

Subjects without complete data will not be included in the comparative analysis of the oral accessibility scores. They will be described and compared to subjects with complete data.

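### The primary comparison excludes patients for a reason tied to its own outcome, so the estimated gain with the OAS applies only to those who tolerated both examinations and is probably too favourable

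*Protocol*

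**What the plan says.** Section 9.1 compares the two examinations by a McNemar test on the share of patients scoring at least 8 and by a paired t-test on the mean score. Section 9.5 limits who enters: "Subjects without complete data will not be included in the comparative analysis of the oral accessibility scores". Section 9.7 repeats the rule. For those left out, 9.5 adds only this: "They will be described and compared to the subjects with complete data".

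Section 5.3.1 gives one premature-stop criterion: "It is impossible to perform the evaluations, without and then with the spatula, due to patient behavior that involves their physical integrity", identified with a Venham score of 5. It continues: "Patients with a score of 5 on the Venham Scale will be examined outside the study". Section 5.3.3 plans for 10% drop-out without replacement.

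The inclusion criterion in 5.1 is a "Score of 2 or more on the Venham Scale on a gradual approach to the oral cavity of the person", with no upper limit. The score has a value for failed access: in the Primary Endpoint row of the protocol summary, "this score ranges from 0 = no accessibility to 12 = total accessibility". In 4.4.1 an item is 0 when neither side can be seen or probed. Annex 6 describes Venham 5 as a patient who shuts the mouth and clenches the teeth.

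**The concern.** The study is one visit of about 30 minutes with no follow-up, so data will seldom be incomplete for the usual reasons. The stop criterion that the protocol names is a behavioural reaction that closes the mouth, and oral access is what the primary endpoint measures. Whether a patient is analysed therefore depends on the outcome.

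The patient who matters most reached 8 or more by hand and then became unmanageable when the OAS was introduced. That is a discordant pair against the device. If the record counts as incomplete, the pair disappears from both tests. Under that reading, a device that provokes many such stops would show the same gain as one that provokes none. Describing the excluded patients makes them visible but does not put them back into the estimate.

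**Working it through.** **Inputs from the protocol.** Share scoring at least 8: 20% without and 40% with the OAS (9.2). Number included: 200 (9.2). Drop-out: 10% (5.3.3). Order fixed, standard examination first (4.2, 4.3).

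**The plan's own sample size.** The 140 patients in 9.2 cannot be reproduced from the stated inputs. For a two-sided McNemar test with difference d = 0.20 and discordant share pd, n = [1.96·√pd + 1.2816·√(pd − d²)]² / d². This gives 49 at pd = 0.20 (no patient loses access), 112 at pd = 0.44 (independent results) and 154 at pd = 0.60 (the maximum). About 140 needs pd near 0.55, which the protocol does not state. Drop-out alone gives 140/0.9 = 156; the rest of the rise to 200 is an unquantified allowance for centre and investigator effects. Nothing below depends on the 140.

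**Assumptions.** The completers show exactly 20% and 40%, and the excluded share is m = 0.10. Of 200 patients, 180 complete: 36 reach 8 or more by hand and 72 with the OAS. The complete-case gain is 20 points. The 20 excluded patients are put back in three ways.

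1. *Both examinations fail.* Gain = (1 − m)·0.20 = 0.18. Counts: 36/200 (18%) against 72/200 (36%). The added pairs are concordant, so the McNemar statistic does not change; only the absolute gain is diluted.
2. *Standard examination scored, OAS examination attempted and stopped.* With q the share of these patients at 8 or more by hand, gain = (1 − m)·0.20 − m·q.
3. *Standard examination stopped, OAS never attempted.* With r the share who would have reached 8 or more with the OAS, gain = (1 − m)·0.20 + m·r.

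| Case | Without OAS | With OAS | Gain (points) |
| --- | --- | --- | --- |
| Complete cases | 36/180 = 20% | 72/180 = 40% | 20 |
| 1 | 36/200 = 18% | 72/200 = 36% | 18 |
| 2, q = 0 | 36/200 = 18% | 72/200 = 36% | 18 |
| 2, q = 0.2 | 40/200 = 20% | 72/200 = 36% | 16 |
| 2, q = 1 (extreme) | 56/200 = 28% | 72/200 = 36% | 8 |
| 3, r = 0 | 36/200 = 18% | 72/200 = 36% | 18 |
| 3, r = 0.4 | 36/200 = 18% | 80/200 = 40% | 22 |
| 3, r = 1 (extreme) | 36/200 = 18% | 92/200 = 46% | 28 |

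**Effect on the test.** Assume 40 gains and 4 losses among the completers (the protocol gives no discordance). Case 2 with q = 0.2 adds 4 losses: 40 against 8, exact McNemar p = 0.000003. Case 2 with q = 1 adds 20 losses: 40 against 24, p = 0.060. With no losses among completers the same extreme gives 36 against 20, p = 0.044.

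**Sensitivity to the drop-out rate.** With 20% excluded, case 1 gives 16 points, case 2 gives 12 at q = 0.2 (range 16 to −4), and case 3 gives 16 to 36.

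**The case against.** There is a good case on the other side, and much of it limits the point.

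- *A reader might infer that every examination that could not be completed is dropped.* The protocol does not define complete data. An attempted examination with no access can be scored 0 under 4.4.1 and kept. This stands, but it leaves the primary result to how each site records a stop.
- *A reader might infer that the gain is certainly overstated.* Because the order is fixed, a patient stopped at the standard examination may never receive the OAS. That result is unobserved and could move the gain either way, as case 3 shows. The wording of 5.3.1 can also be read as neither examination being possible, which leaves the McNemar test unchanged.
- *A reader might infer that such losses are frequent, since 5.1 has no upper Venham limit.* The only figure given is the planned 10%. A patient already at 5 on approach may leave before either examination, which says nothing about the OAS.
- *A reader might infer that the worst Venham results are excluded too.* The rule in 9.5 and 9.7 names only the accessibility scores. Section 4.2 has Venham recorded at each examination, and no sentence removes those values from the tolerability analysis.
- *Part of the problem is already handled.* Section 11.2 requires an explanation for each missing value, and incomplete subjects are described and compared. There are also other routes to incomplete data: refusal by the patient (4.2) and withdrawal by the legal representative (12.5).

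What survives is that a stated rule, given twice, makes inclusion in the primary comparison depend on the outcome, and no planned analysis counts stopped patients as failures.

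**Conclusion.** The point holds in limited form and should be fixed; confidence is moderate. The complete-case gain applies to patients who tolerated both examinations and is probably too favourable. At the planned 10% exclusion, the moderate cases put the gain in all included patients at 18 or 16 points where the analysis would report 20, a relative overstatement of 11% (20/18) to 25% (20/16). The bounds are 8 points if every excluded patient was accessible by hand and failed only with the OAS, and 28 if every excluded patient was stopped by hand and would have succeeded with it.

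The documents do not support saying that significance would be lost. The p = 0.060 result needs all 20 drop-outs to have scored 8 or more by hand, which puts the by-hand rate at 28% against the protocol's 20%, and it also rests on 4 assumed losses among completers. The moderate case leaves the conclusion unchanged. All these figures rest on completers matching the 20% and 40% hypothesis and on assumed patterns of failure.

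**What to change.** In 9.5 and 9.7:

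- Include in the primary analysis every eligible patient who started the first examination.
- Score as 0 (below 8) an examination that was attempted but stopped or prevented by the patient's behaviour.
- For an OAS examination never attempted, show the result over a range from all failing to all succeeding. Do not impute a Venham value: giving these patients a score of 0 and a Venham of 5 would invent data.
- Keep the complete-case comparison as a sensitivity analysis.
- Report the number of stops by behaviour separately for each examination, using the reasons for missing data that 11.2 already requires.

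Reconcile 5.1 (Venham 2 or more, no upper limit) with 5.3.1 (score 5 examined outside the study), because together they decide who is in the denominator. Which rule applies is for the sponsor and investigators to settle.

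The cost is wording in two sections and one extra summary table. The reported gain may be somewhat smaller, and it will carry a range if some patients never reach the OAS examination.

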**9.6. management of amendments to the original analysis plan**

No special management is foreseen.

Any amendments must be the subject of an explicit discussion between the investigator and the methodologist.

**9.7. choice of people to include in the analyses.**

Subjects without complete data will not be included in the comparative analysis of the oral accessibility scores. They will be described and compared to subjects with complete data.

**10. ACCESS rights TO DATA AND SOURCE DOCUMENTS**

All data and information concerning the patient will remain strictly confidential. The persons with direct access in accordance with the current laws and regulations, in particular Articles L.1121-3 and R.5121-13 of the Public Health Code (for example, investigators, those in charge of quality control, the monitors, the clinical research assistants, the auditors, and all people who collaborate in the trials), will take all necessary precautions to ensure the confidentiality of information relating to the investigational drugs, the trials, and the persons who participate (particularly with regard to their identity and the results that were obtained). The data collected by these people during quality controls or audits are then made anonymous.

**11. QUALITY Contrôl and assurance**

**11.1 Monitoring**

The risk level assigned to the study, which is defined on the basis of the OPTIMON table (Appendix 8), is B (Class I device not marked with CE). According to the Logistics-Impact-Resources score of the DRCI's "Quality of Promotion" working group (Annex 9), a MINIMAL level of monitoring will be necessary.

The Clinical Research Assistant who represents the sponsor will visit the investigative center at the pace of MINIMAL level monitoring:

- Site-opening visit: this will occur before the 1st inclusion to set up the protocol and become familiar with the various stakeholders participating in the biomedical research.

- During subsequent visits, only consent will be monitored. If consent is non-compliant, the patient records will be monitored randomly at the site.

The sheets of the case report forms will be separated and retrieved by the Clinical Research Associate.

The principal investigator as well as other investigators who include or monitor the study participants commit to meeting the Clinical Research Associate at regular intervals.

During these site visits, and in accordance with Good Clinical Practices, the following elements will be reviewed:

- Compliance with the protocol and the procedures in the research,
- Examination of the source documents: notification that the patient file contains a signature indicating the patient's consent or the consent of the holders of parental authority or the patient’s guardian.

- Closing visit: retrieval of the last sheets from the case report forms and the inventory records of the pharmacist and archiving of the biomedical research documents.

As such, the investigator agrees to make the following available to the Clinical Research Associate during his/her monitoring visits:

 The medical records of the patients

 The case report forms

 The forms that include the consent of the patients.

### 11.2 Completion of data in the case report form

All information required by the protocol must be provided in the case report form and the investigator must provide an explanation for each missing data point.

The data will have to be transferred to the case report forms as they are obtained, regardless of whether they are clinical or paraclinical data. The data will have to be copied into the case report forms with clear and legible writing in black ink (to facilitate duplication and computerization).

The erroneous data found in the case report forms will be crossed out clearly and the new data will be copied into the case report form along with the date and initials of the investigative team member who made the correction.

The anonymity of the subjects will be ensured by a code number and the research participant’s initials on all research documents, or by redacting by appropriate means the personal data of the patients on the copies of the source documents that will be used for research documentation.

The computerized data will be placed in a file and declared to the CNIL according to the procedure adapted to each case.

**12. ETHICAL AND REGULATORY Considérations**

The sponsor and the investigators agree to ensure that this research is conducted in compliance with Law 2004-806 of 9 August 2004 and in agreement with Good Clinical Practices (ICH version 4 produced on 1 May 1996 and settled on 24 November 2006) and the Declaration of Helsinki (Ethical Principles for Medical Research on Human Subjects, Seoul 2008).

The research is conducted in accordance with the present protocol. The investigators commit to adhering to the protocol in all respects, especially with regard to collecting consent and notifying the authorities and following up serious adverse events.

Each investigator will agree to respect the obligations of the law and to conduct the research according to Good Clinical Practices amd the terms of the current Declaration of Helsinki.

12.1 Request for authorization from the ANSM

To be able to start the research, the sponsor must submit an application file for authorization by the competent authority, namely, the ANSM. The competent authority defined in Article L.1123-12 makes decisions regarding the safety of persons who participate in biomedical  research. In particular, they assess the quality and safety of the products that are used during the research and ensure that, where applicable, they are used according to current standards and their terms of use. The competent authority also assesses the safety of persons with regard to the acts performed, the methods used, and the planned monitoring procedures in the study.

12.2 Request for advice from the Ethics Committee

In accordance with Article L.1123-6 of the Public Health Code, the research protocol must be submitted by the sponsor to an Ethics Committee. The sponsor will inform the competent authority about the opinion of the Ethics Committee before the start of the research.

12.3 Amendments

The amendments must be categorized as substantial or not substantial.

A substantial amendment is a change that could, in one way or another, modify the guarantees to the persons who participate in the biomedical research (modification of an inclusion criterion, extension of the inclusion period, participation of new centers, ...).

After beginning the research, any substantial amendment by the sponsor must obtain, before its implementation, a favorable opinion and authorization from the competent authority. In this case, and if it is deemed necessary, the committee will ensure that the people involved in the research provide new consent.

In all cases of substantial amendment, the sponsor must request authorization from the ANSM and/or request an opinion from the Ethics Committee.

12.4 CNIL déclaration

This research falls within the framework of "Reference Methodology" (MR-001) in accordance with the provisions of Article 54 (paragraph 5) of the modified Law of 6 January 1978 that relates to data processing and liberties. This modification was approved by the decision of 5 January 2006. The CHR of Metz-Thionville signed a commitment to comply with "Reference Methodology".

Only the data needed for the research will be collected. The patient nevertheless has the right to oppose the automated processing of the data concerning him/her. The patient will have the right to access the data concerning him/her at any time. He/she will also have the right to request the rectification of inaccurate data or data that has become inaccurate. He/she will be able to exercise their rights with [name], the coordinating investigator.

For all information of a medical nature, the rights of the patients may be exercised directly or *via* the doctor of their choice.

In the case where the consent was given by the family (or authorized person), only the patient is able to access the data concerning him/ her as described above.

**12.5 Participant information sheet and Informed consent**

The study population consists of people who have a particularly protected status in terms of biomedical research. In other words, the adult patients are subject to a legal protection order as well as the minor patients.

- **For adult patients under guardianship and minor patients:**

Before obtaining the consent of the legal representative or the holders of parental authority over the patient, the investigator agrees to provide the patient with information on the proposed study that is as clear, honest, appropriate, and complete as possible; the investigator also gives the patient a participant information sheet that is adapted to their ability to understand.

The information is also delivered:

- To the holders of parental authority over minors
- the legal representatives of minors and adults who are under guardianship

The information relates to:

- the objectives and limitations of the study for the patient
- the right of the legal representative to refuse to have the patient participate in the study
- the right of the legal representative to have the patient leave the study at any time

When the substance of the information has been given to the patient and the legal representative of the patient and when the investigator has ensured that the latter understands the implications of the participation of the patient in the trial, the written consent of the legal representative will be collected by the investigator. The patient's personal commitment will always be sought.

Two original copies of the consent form will be signed by the holders of parental authority or the guardian and the investigating doctor:

 A copy will be given to the holders of parental authority or the guardian, as the case may be

 One copy will be kept and archived by the investigator.

- **For adult patients under trusteeship**:

The patient, assisted by his/her trustee, will receive oral and written information that is clear, honest, complete and adapted to his/her ability to understand.

If the patient agrees to participate in the study after having had time to reflect and having had the opportunity to ask all the questions he/she wishes, the patient, with the assistance of his/her trustee, may sign his/her own consent form in two original copies. A copy will be given to the patient and the 2nd will be kept and archived by the investigator.

